**FIGURE 5 F5:**
[figure not shown]
Study activities.

This intervention is expected to promote the following outcomes; Participation in the experimental group will result in a significant decrease in stigmatizing attitudes among PHC providers toward individuals with MISUI compared with the control group as measured by the Chilean version of the OMS-HC; Participation in the experimental group will result in a significant decrease of PHC users experiences of stigma conveyed by PHC providers compared with the control group as measured by the ISMI scale, validated for the Chilean population; The changes in attitudes and behaviors within the experimental group will be sustained over time as measured at 6 months-follow-up.

### Data analysis

The data analysis will be conducted through months 42–48. Post data collection activities consider the following: (1) Data cleaning and evaluation, (2) Creation of derived variables, (3) Response rate calculation and (4) Bias evaluation.

It will be carried out using SAS 9.4 (specifically, using POC MIXED and PROC GENMOD) and R 3.5. Mixed-effect modeling will used for both PHC provider and user data, which will include individuals and CESFAMs as random effects and group (intervention/control) as fixed effects. The technique is appropriate to analyze cluster randomized controlled trials because these models can account for the possible dependence between responses of users and PHC providers within the same CESFAM. A descriptive analysis will initially be conducted to obtain a general picture of the sample. Time and important covariates (e.g., demographics) as they relate to our outcome variable will be explored. Univariate association tests will be performed to clarify the unconditional effect of these covariates on outcomes.

After the quantitative and qualitative data have been analyzed, summarized, and interpreted independently, the primary focus of the integrated analysis will be on identifying and discussing to what extend and in what ways the qualitative results help to explain the quantitative results (explanatory design). Implementing a “hybrid” approach (104) that will be used for qualitative data.

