#### Specific objective 3: Evaluate the effectiveness of the intervention in primary health care

This part of the interventions is composed by a quantitative and a qualitative component.

1. a Quantitative Component:

All PHC providers at the selected CESFAMs who have direct contact with users will be recruited for the study and will be expected to participate at all data collection time-points. A total sample size of at least 36 PHC providers per CESFAM with a total of 288 per arm its estimate (or 576 per data collection). Sample size for the proposed study was calculated in two steps. First, it was calculated with individual randomization. This calculation was based on the mean ± SD score for the OMS-HC scale was 48 ± 8.3 points, estimated with a sample of 798 PHC providers surveyed in FONDECYT N° 1160099 (34). This should be the average obtained in control CESFAM for the present study. Based on prior interventions in Canada (63), an estimated effect size of 10% in the intervention arm and a placebo effect of 3% in the control arm (from survey application) is expected. Thus, the average OMS-HC score in the intervention arm is expected to decrease to 43.2 ± 8.3 in the intervention group and 46.6 ± 8.3 in the control group (representing a decrease of 4.8 and 1.4 points, respectively). The standard deviation was assumed to remain the same in the intervention and calculations. To detect a statistically significant difference between intervention and control CESFAM, with an α = 5% and statistical power of 80%, the minimum sample size per arm is 94 individuals. Considering a 10% loss to follow-up in the intervention arm, 105 individuals per arm should be recruited with an individual randomization design. The minimum sample size was also calculated considering cluster randomized controlled design. Two elements were considered: (1) a minimum sample size of 105 and (2) an estimation of the intracluster correlation coefficient (ICC) for the study outcome (OMS-HC scale) (83). In this case, it was assumed the ICC to be ρ = 0.05, which is consistent with highest value reported in the literature for outcomes in primary care settings (74) and slightly higher than that reported in a study of a depression program in CESFAMs in Chile (84). Given the required sample size calculated based on individual randomization and the value of ICC = 0.05, the minimum number of clusters required is equal to: [105*0.05] = 5 clusters (75). However, a larger number of clusters would allow recruitment of a smaller number of individuals per cluster, maintaining an α = 5% and statistical power of 80% to detect differences between the control and intervention groups (85). For example, if 8 clusters per arm is considered (16 CESFAM total), it is necessary to recruit a minimum of 36 professionals per CESFAM. Thus, a minimum of the total sample of PHC providers to recruit would be 288 per arm (576 total). The validated, Chilean version of the Opening Minds Scale for Health Care Providers Scale (OMS-HC) (86), will be used as the primary outcome measure for PHC Professionals in the study. It will be applied at baseline, mid-point, end-point, with an expected 9-month interval between applications, and at 6-month follow-up.

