
A self-administered questionnaire will be used to examine stigma directed at persons with MISUI among health professionals. Five existing scales to measure stigma toward MISUI were selected to include in the questionnaire because they had been validated in Chile and were recommended by the research team. These scales reflect the current state of knowledge about stigma measurement (with a focus on health providers and persons with MISUI), as well as the feasibility of implementation at CESFAMs. They include: the Opening Minds Scale for Health Care Providers OMS-HC (83, 87, 88), Mental Illness: Clinicians’ Attitudes (MICA) (89), Modified Bogardus Social Distance Scale (90, 91) or Grandon Social Distance Scale (92), Recovery Scale for Providers (RS) (93), and the Recovery Self-Assessment-Revised (RSA-R) scale (94).

This questionnaire will be completed at four time-points (baseline, mid-point, end-point, and 6-month follow-up). It will collect data related to two main components: (1) socio-demographic and other relevant general variables; and (2) attitudes toward MISUI stigma and recovery. The end-point questionnaire will also include a third component focusing on the intervention and its implementation. A self-administered questionnaire will be provided to PHC providers at each CESFAM (intervention and control) at a time set aside by CESFAM directors.

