CESFAM users will be recruited for participation in baseline and end-point data collection regarding their experiences of stigma by PHC providers. These users must be over the age of 18, have received treatment for MISUI at the CESFAM in the 3 months prior to participation (though not necessarily by a mental health professional), and have a MISUI diagnosis. User MISUI may be diagnosed by a health practitioner or self-diagnosed. Since stigma is a barrier to seeking and receiving help, it is important to include participants who have not been formally diagnosed by a healthcare provider. A research team member will approach users at the waiting room and screen them for inclusion and exclusion criteria. Users in capacity to consent will be invited to sign the consent form and those who sign will be part of the face-to-face survey assisted by a research team member on the same day in the same health facility. To assess capacity to consent, a Spanish adaptation of dimensions and criteria of the Macarthur Competency Assessment Tool for Clinical Research (MACCAT-CR) (95) are used. This process includes the following actions; (1) The interviewer exposes the user to the relevant information of the project after which he/she is questioned about what has been explained (comprehension); (2) Subsequently, they are asked about their appreciation or assessment of the information provided in their specific circumstances; and (3) A reasoned reflection on the decision to be made is promoted, assessing the circumstances and consequences, to end up expressing their choice.

The primary outcome for users will be measured using The Internalized Stigma of Mental Illness (ISMI) scale, validated for the Chilean population (96). The study will collect cross-sectional samples at baseline and end-point data collection and compare average scores between intervention and control groups for baseline and end-point measures.

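### The stated mixed model names group as its only fixed effect, so across several waves it does not estimate the post-intervention difference that sized the trial

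*Protocol article*

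**What the plan says.** The Data analysis section specifies one mixed-effects model for provider and user data, "which will include individuals and CESFAMs as random effects and group (intervention/control) as fixed effects". The Methods part of the abstract says the same. Time appears once, after the model and next to the descriptive analysis: "Time and important covariates (e.g., demographics) as they relate to our outcome variable will be explored". No interaction, baseline adjustment or primary time-point is stated.

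Under Specific objective 3, the provider outcome (OMS-HC) has four waves: "It will be applied at baseline, mid-point, end-point, with an expected 9-month interval between applications, and at 6-month follow-up". Users are sampled cross-sectionally at baseline and at end-point, and the plan there is to "compare average scores between intervention and control groups for baseline and end-point measures".

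The provider sample size rests on a post-intervention difference. Scores are "expected to decrease to 43.2 ± 8.3 in the intervention group and 46.6 ± 8.3 in the control group", a gap of 3.4 points. The user sample size rests in the same way on 10.23 against 8.79. The expected outcomes listed at the end of Specific objective 3 are a greater decrease than in control for each population, and changes that last to the 6-month follow-up.

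**The concern.** A random effect for individuals has a purpose only if repeated records on the same person enter one model. For providers this implies that the waves are modelled together. With group as the only fixed effect, the group coefficient is then the between-arm difference averaged over all waves. One of those waves is before the intervention, where randomization makes the expected difference zero. Another is half-way through an 18-month programme in which some activity is scheduled only from month 7. The result is not the quantity the trial was sized for, and no term in the model separates end-point from follow-up.

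For users, the same model applied to both cross-sections would average a baseline difference of zero with the end-point difference. Users are not followed as individuals, so an individual random effect has nothing to identify it. If the model is followed as written, the main analysis has less power than planned and leaves the persistence hypothesis without a test.

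**Working it through.** **Reproducing the plan's figures** (two-sided 5%, 80% power; n = 2(1.960 + 0.842)²σ²/δ² per arm)

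- Providers: σ = 8.3, δ = 46.6 − 43.2 = 3.4. n = 93.5, so 94, as stated. 94/0.9 = 104.4, so 105. With ICC 0.05 and 8 clusters per arm, m = 105 × 0.95/(8 − 105 × 0.05) = 36.3, against 36 stated.
- Users: σ = 4.74, δ = 14% of 10.34 = 1.4476. n = 168.3, so 169, as stated (the rounded 1.44 gives 171). With ICC 0.01, m = 169 × 0.99/(8 − 169 × 0.01) = 26.5, so 27.

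The sample sizes are not in dispute.

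**What a group-only model estimates.** With equal wave sizes, the group coefficient is the mean over waves of the between-arm differences.

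- Providers, relative effects (0, 1, 1, 1): 0.75 × 3.4 = 2.55, a 25% cut.
- Providers, relative effects (0, 0.5, 1, 1): 0.625 × 3.4 = 2.13, a 37.5% cut.
- Users, relative effects (0, 1): 0.5 × 1.4476 = 0.72, a 50% cut.

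In 400 simulated trials, the group-only estimates averaged −2.11 (providers, half effect at mid-point) and −0.71 (users). The end-point-versus-baseline contrasts averaged −3.41 and −1.42.

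**Power** (noncentral t, 16 − 2 = 14 df)

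*Providers.* I use the unrounded difference, 7% of 48 = 3.36, and m = 36 × 0.9 = 32.4 after the planned 10% loss. Between-cluster variance is 0.05 × 8.3² = 3.44; within-cluster variance is 0.95 × 8.3² = 65.45. The within-person correlation r is not in the protocol; I assume 0.3 to 0.7.

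- End-point only: SE = √[(2/8)(3.44 + 65.45/32.4)] = 1.169; power 76%.
- Four waves pooled: SE = √[(2/8)(3.44 + 65.45(r + (1 − r)/4)/32.4)], from 1.049 (r = 0.3) to 1.119 (r = 0.7).
- Effect 0.75 × 3.36 = 2.52: power 61% to 55%.
- Effect 0.625 × 3.36 = 2.10: power 46% to 42%.

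Using 3.4 in place of 3.36 raises each figure by about one percentage point.

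*Users.* Between-cluster variance is 0.01 × 4.74² = 0.225; within-cluster variance is 22.24.

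- End-point only: SE = √[(2/8)(0.225 + 22.24/27)] = 0.512; effect 1.4476; power 75%.
- Both waves pooled: SE = √[(2/8)(0.225 + 22.24/54)] = 0.399; effect 0.72; power 39%.

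Doubling the observations does not make up for halving the effect.

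**Individual random effect for users.** The protocol describes separate cross-sections whose members need not be the same people, and makes no allowance for loss to follow-up. With essentially one score per user, person variance and residual variance cannot be separated.

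**The case against.** The best defence is that the sentence says what the model will include, not that it includes nothing else. The next lines mention time, and an article may leave time coding, interactions and further random effects to a full protocol or SAP that is not shown. This stands in part: the article does not exclude time, and it never says which waves enter the model, so pooling is inferred. But the article does state an effectiveness model, twice and in the same terms, and gives time only an exploratory role. For providers, the individual random effect makes joint modelling of the waves the natural reading.

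For users the defence is stronger. Specific objective 3 can be read as a comparison at each wave, in which case the end-point contrast is the planned one. A reader might infer that the user effect is certainly halved; the document does not support that. A reader might also infer a fixed loss of about a third for providers. The protocol gives no mid-point effect, so only the conditional figures hold.

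Two further inferences should not be charged to the plan: inflated type I error from omitting CESFAM-by-time variation in a change contrast, and low power of a difference-in-differences for users. Both concern models the protocol does not state, and the first also needs correlations it does not give.

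**Conclusion.** The concern holds in conditional form. As stated, the model's group coefficient is not the post-intervention difference behind the sample size whenever several waves are fitted together, and it cannot address persistence.

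- **Providers:** a cut of 25% (power about 55–61% against 76%) or 37.5% (about 42–46%). The 25% figure is the smallest cut if the effect never exceeds the planned one at any wave.
- **Users:** either the effect is halved (power about 75% to 39%), or the analysis under Specific objective 3 differs from that under Data analysis. Either way, the individual random effect does not suit cross-sectional samples.

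The figures assume equal wave sizes, no baseline difference, a full effect at end-point (and, for providers, at follow-up), an assumed within-person correlation of 0.3–0.7, and cluster effects that are constant over time.

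**What to change.** State the primary model with group, categorical time and group-by-time as fixed effects, or model post-baseline outcomes adjusted for baseline (for users, who have no individual baseline, the CESFAM baseline mean). Name the between-arm difference at end-point as the primary contrast and the between-arm difference at 6 months as the test of persistence for providers. Keep the individual random effect for providers only. Where several waves are modelled together, add a CESFAM-by-time random effect to the CESFAM effect. Bring the abstract, the user paragraph under Specific objective 3 and the Data analysis section into agreement.

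The cost is analysis wording only. No new data or change in sample size is needed, and the change can be made before the analysis scheduled for months 42–48.

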## Discussion

This study represents a new stage of relevant and innovative research in mental health and stigma in Chile that will contribute to improving access and quality of care for people with MISUI. Evaluating the impact of the intervention model and its implementation will provide the necessary basement to scale the intervention up to other CESFAMs across Chile. This intervention is vital to fight stigma toward MISUI and other conditions in PHC and the Chilean health system overall. Knowledge translation will be a special focus of this study, in order to communicate results to local, national, and international audiences. It is also important to evaluate the feasibility of the intervention scale up, since different studies have reported cultural influences on mental illness-related stigma (105).

Stigma has a detrimental effect on health policies (106), treatment outcomes (107), and efficient and effective recovery from mental health problems (23). Evidence indicates that stigma reduction initiatives must be comprehensive, multifaceted, and able to target various levels within a setting. Different strategies to address stigma have been suggested (66, 69). At the organizational level, specific interventions implemented across entire institutions (e.g., workplaces) (108) may provide supportive environments that encourage anti-stigmatizing practices (109). It has been suggested that reducing stigma interventions with people already in contact with health services, as people with MISUI, needs alternative strategies to deal with self-stigma and cope with experienced stigma to facilitate adherence (46). That reinforces the importance of a collaborative approach, where service users and healthcare practitioners work toward destigmatize PHC. Healthcare professionals stigmatizing behaviors and beliefs may be subtle and denied because of how they are perceived (23) thus, it is important to implement interventions focusing on awareness, internal policies, procedures and protocols. It’s also relevant to implement educational approaches, as the one included in this protocol, as adequate information and contact between the public and the stigmatized individuals would lead to diminish stigma (110) in PHC settings.

This study has some particular limitations and potential bias: (a) Non-response bias: A survey of this kind will invariably tend to select the more cooperative and communicative respondents, who may also be more tolerant. Different strategies have been considered to increase the response rate, even among people who might have more stigmatizing attitudes. In particular, it is important to consider potential item non-response as a limitation of this study. The research team will emphasize respondents the importance of trying to answer all the questions and some alternatives, like mean substitution or other imputation methods, will be used if is necessary; (b) Social desirability bias: As with other measurement approaches, there are potential biases measuring stigma attitudes, because it might be considered a sensitive issue. Self-administered questionnaires expect to reduce this bias, as well as the respect for confidentiality and use of the MCSDS (100); (c) Difficulties to measure attitudes: It can be difficult translating untouchable concepts into variables; (d) External validity is threatened by the limitations of the sample, the generalizability of the results are limited to the target population (CESFAM PHC Providers); (e) Inferring behavioral responses from reported intentions; (f) Non-blinding: Participants will not be blinded. Since the intervention is an RCT, this may be a bias source.

Some of the main strengths of this study include: (a) There is a real public health need for this intervention study: stigma is a key factor that affects people with MISUI, resulting in their reluctance to seek health care services. This study will be one of the first to intervene to reduce stigma among PHC professionals in Chile. As discussed in Background, prior stigma reduction intervention work has found that reducing MISUI stigma in PHC has the potential to increase access to care for user with these conditions, improve their quality of life, and contribute to improved treatment adherence for MISUI. (b) The use of a census/organizational approach: seeks to change organizational culture and stigma toward those with MISUI *via* contact-based education, structural policy change, and raising awareness at the CESFAM level. (c) Cultural appropriateness: Special efforts will be made to adapt the intervention for this context, and the stigma instruments were adapted to the Chilean context in FONDECYT 1160099. The mixed methods approach of this research allows addressing many of the limitations of the quantitative stigma measures and facilitates deep understanding of intervention’s impact and implementation. (d) The inclusion of both health providers and users in this study: Many studies of stigma in PHC have not included the perspective of users, limiting the impact of their results in the lives of people with MISUI.

After a critical analysis of the proposed study, it is possible to say that its design and internal validity are sufficiently strong and that special measures have been taken to control and reduce its potential limitations. Finally, it is important to remark that “stigma” has many sources and this study will not be able to tacked all of them (e.g., media, social services, the educational system, and legislation). While recognizing stigma as a complex concept, this study seeks to reduce stigma at the health services level by an innovative and collaborative approach. Having that in mind, this will be a unique relevant study to test an innovative anti-MISUI stigma intervention targeting CESFAM providers in Chile from an organizational perspective.

## Ethics and dissemination

a. Research Ethics Approval

This protocol and the template and site-specific informed consent forms, recruitment materials and other requested documents were reviewed, analyzed and approved by the sponsor and the applicable Pontificia Universidad Católica de Chile Ethics Committee (EC) (ID::190603010), Herminda Martin de Chillán Hospital EC, Valparaiso Health Service EC, Coquimbo Health Service EC and Reloncavi Health Service with respect to scientific content and compliance with applicable and intervention research and human subjects regulations. The proposal will follow all ethical guidelines provided for conducting research with human beings. The proposal, interim reports and final reports will be submitted to the EC’s at the beginning, middle, and end of the study.

b. Consent

All participants will be required to read and sign an informed consent form outlining the aims and objectives of the study prior to engaging in any aspects of the project, particularly before participating in the data collection process. It will be presented comprehensibly, the opportunity to ask questions will be given, understanding confirmation will be solicited, and voluntarily participation will be re assured. All user participants will also receive an oral explanation of the consent process prior to signing and/or agreeing to participate, and PHC user capacity to consent will be considered.

Informed consent will be conducted by interventors/researchers/PHC workers, guaranteeing adequate training and experience, in order to protect participants moral wellbeing and human rights. The consent process will be conducted by trained professionals.

c. Confidentiality

All participants will be assigned a numerical code, resulting in the anonymization of data. All knowledge translation materials will only include data for groups with 10 members or more to protect confidentiality. Although the quantitative surveys include a question about the participant’s CESFAM, reports for each CESFAM will be general and will not include a separate analysis by profession, limiting the potential to identify individual respondents.

d. Ancillary and Post-Trial Care

This study involves minor risk of potential harm (physical, emotional and/or social), however, specific measures will be taken to minimize them: (1) confidentiality, so participants will not be treated differently than other PHC providers/CESFAM as a result of their responses; (2) participation is voluntary and no negative consequences will result for those who decide not to participate; (3) participants may skip any/all questions they do not want to answer as part of the mixed methods approach; (4) information is provided to all participants regarding the institutions conducting the research, the principal investigators, and contact information and active referral for psychosocial support when needed for those who may be emotionally triggered by participating; and (5) final results will be shared with participants.

e. Dissemination Policy

The research team conceptualizes dissemination as a key component of a comprehensive knowledge translation approach (111) in a dynamic ongoing cycle. Special efforts will be made in all the stages of the project to make research results accessible to various audiences (such as research participants, *Servicios de Salud* and CESFAM authorities, Chilean Ministry of Health, and the academic community) through resources such as a research portfolio, reports, at least three academic papers, meetings, and at least two academic conference presentation, as well as to explore possibilities like articles and features in local mass media (e.g., radio, television, and newspapers). There will be a specific budget that supports dissemination efforts. Each academic or research report, will be reviewed by project research committees and by peers, prior to submission to evaluate methodology and implementation and appropriateness merits. The study results will be released to the participating PHC workers and users.

